## Abstract

**Background:**

Regorafenib is an oral multikinase inhibitor for metastatic colorectal cancer (mCRC) previously treated with fluoropyrimidines, irinotecan, oxaliplatin, monoclonal antibodies targeting vascular endothelial growth factor, and monoclonal antibodies targeting epidermal growth factor receptor. A dose reduction from 160 mg to 120 mg regorafenib reduces regorafenib-associated adverse events (AEs). Dose adjustment of irinotecan in a 5-fluorouracil/leucovorin/irinotecan (FOLFIRI) regimen on the basis of an individual uridine diphosphate glucuronosyl transferase 1A1 (*UGT1A1)* genotype provides optimal oncological outcomes with acceptable AEs. The aim of this study is to address the efficacy and safety of a dose-adjusted combination of regorafenib and FOLFIRI for patients with mCRC.

**Methods:**

A prospective, multicenter, randomized in a 2:1 ratio, controlled, clinical trial with two parallel arms will be conducted to compare irinotecan dose-escalated FOLFIRI according to *UGT1A1* genotyping plus 120 mg regorafenib with 120 mg regorafenib alone in previously treated patients with mCRC. The primary endpoint is progression-free survival, and the secondary endpoints are overall survival, disease control rate, time to progression, and duration of treatment. Safety assessments will also be recorded.

**Discussion:**

Dose adjustment for regorafenib and irinotecan makes treatment-related AEs tolerable and makes the concomitant treatment practicable. This study will provide initial evidence regarding the efficacy and safety of a new combination of chemotherapy and a targeted agent for mCRC.

**Trial registration:**

ClinicalTrials.gov, NCT03880877. Prospectively registered on 19 March 2019.

## Background

Regorafenib monotherapy is currently the third- or fourth-line standard of care for patients with metastatic colorectal cancer (mCRC) who have been previously treated with fluoropyrimidines, irinotecan, oxaliplatin, and monoclonal antibodies targeting vascular endothelial growth factor (VEGF), and monoclonal antibodies targeting epidermal growth factor receptor (EGFR) for those with *KRAS* wild-type cancers. Regorafenib targets and inhibits membrane-bound and intracellular receptor tyrosine kinases (RTKs) that are involved in signaling for oncogenesis, angiogenesis and proliferation of cancer [1]. The global CORRECT trial demonstrated that regorafenib monotherapy had significantly better progression-free survival (PFS; 1.9 versus 1.7 months, *P* < 0.001), overall survival (OS; 6.4 versus 5.0 months; *P* = 0.0052), and disease control rate (DCR; 41% versus 15%, *P* < 0.0001) in previously treated mCRC [2]. Similarly, the CONCUR study, which was conducted in Asians, also yielded significant differences in PFS (3.2 versus 1.7 months, *P* < 0.0001), OS (8.8 versus 6.3 months; *P* = 0.00016), and DRC (51.5% versus 7.4%, *P* < 0.0001) [3]. The most frequently encountered adverse event (AE) of regorafenib is hand–foot skin reaction (HFSR), which leads to dose reduction or interruption of treatment in response to the AE. Dose reduction of regorafenib to 120 mg reduces the severity of AEs and allows better patient tolerance and compliance with comparable oncological results [4].

Irinotecan is a prodrug that is converted to its active metabolite, 7-ethyl-10-hydroxycamptothecin (SN-38), which acts on topoisomerase I in vivo to interrupt DNA replication in cancer cells and induce cell death. SN-38 is metabolized and detoxified by glucuronidation of uridine diphosphate glucuronosyl transferase (UGT), mainly the *UGT1A1* isoenzyme in the liver, to SN-38G [5]. The differences in capacity of glucuronidation of *UGT1A1* is determined by the number of repeats in the TATA box on the *UGT1A1* promoter, with the most common *UGT1A1* allele with 6 TA repeats (*UGT1A1**1, wild type) and a variant allele with 7 TA repeats (*UGT1A1**28, mutant type). Individuals with *UGT1A1**28 exhibit reduced *UGT1A1* transcription and expression and consequently reduced SN-38 glucuronidation and increased toxicities of irinotecan [6]. Polymorphisms of *UGT1A1* therefore decide the rate of SN-38 glucuronidation and the following effects on the pharmacokinetics and toxicities of irinotecan [7]. Accordingly, dose adjustment of irinotecan based on individual *UGT1A1* genotyping along with 5-fluorouracil (5-FU) and leucovorin (LV) (FOLFIRI regimen) obtains acceptable AEs along with optimal oncological outcomes [8].

Based on the current literature, concomitant use of chemotherapy and targeted agents in treating mCRC shows potential add-on benefits for tumor control in the front-line setting. In our previous preliminary observational study, in which regorafenib plus FOLFIRI with dose escalation according to *UGT1A1* genotype were administered to previously treated patients with mCRC, we revealed superior oncological effects over regorafenib monotherapy [9]. As the result, the current study aims to explore the efficacy and safety of regorafenib and FOLFIRI concomitant treatment with dose-adjusted irinotecan based on *UGT1A1* genotype in previously treated mCRC patients compared to those who receive regorafenib alone in a prospective, randomized, two-arm, controlled setting.

## Methods/design

### Trial design

This is a multicenter, randomized (in a 2:1 ratio) controlled clinical trial with two parallel arms, as summarized in Fig. 1. Neither the investigators nor the patients are masked to treatment allocation. In order to compare the efficacy and safety of regorafenib plus FOLFIRI with dose-adjusted irinotecan based on *UGT1A1* genotype (study group) and regorafenib monotherapy (control group), a total of 153 patients with mCRC that were previously treated with fluoropyrimidines, irinotecan, oxaliplatin, and monoclonal antibodies targeting VEGF, and monoclonal antibodies targeting EGFR for those with *KRAS* wild-type tumors, will be recruited, of which 102 participants will be assigned to the study group and 51 participants will be assigned to the control group in a 2:1 ratio.

**Fig. 1 Fig1:**
[figure not shown]
Flow diagram for this study. AE adverse event, FOLFIRI 5-fluorouracil/leucovorin/irinotecan, Gr grade, Iri irinotecan, UGT uridine diphosphate glucuronosyl transferase

### Study setting

The study will be conducted in four hospital centers in Taiwan.

### Study participants

Participants will be recruited from Kaohsiung Medical University Hospital, Cathay General Hospital, Taichung Veterans General Hospital and Taipei Veterans General Hospital by the colorectal surgeons. The planned recruitment period is 24 months and informed consent will be obtained from all participants before randomization.

### Eligibility criteria

#### Inclusion criteria

The following inclusion criteria will be used:
Cytologically/histologically confirmed mCRCPatients who have been previously treated with, or are not considered candidates for, other locally approved standard treatment(s) and for whom the decision has been made per investigator’s routine treatment practice to prescribe regorafenib as third-line (*RAS* mutant) or fourth-line (*RAS* wild-type) therapyAged no less than 20 years at the time of acquisition of informed consentEastern Cooperative Oncology Group performance score 0–1Patients with measurable or nonmeasurable disease in the colon or rectum, according to Response Evaluation Criteria in Solid Tumors (RECIST) version 1.1Life expectancy of more than 12 weeksWomen with childbearing potential must agree to perform adequate contraception measures from informed consent until a least 12 weeks after the last study drug administration; the investigators or designee are requested to advise the patient to achieve adequate birth controlAdequate organ and bone marrow function as defined below:
Total bilirubin ≤1.5 × upper limit of normal (ULN)Alanine aminotransferase and aspartate aminotransferase ≤2.5 × ULN (≤5 × ULN for patients with liver metastases)Alkaline phosphatase ≤2.5 × ULN (≤ 5 × ULN for patients with liver metastases)Amylase and lipase ≤1.5 × ULNSerum creatinine ≤1.5 × ULNGlomerular filtration rate ≥30 ml/min/1.73 m^2^, according to the modified diet in renal disease abbreviated formulaInternational normalized ratio/partial thromboplastin time ≤1.5 × ULNPlatelet count ≥100,000/mm^3^Hemoglobin level ≥9 g/dLAbsolute neutrophil count ≥1500/mm^3^Ability to understand and willingness to sign the written informed consent form

#### Exclusion criteria

The following exclusion criteria will be used:
Treatment with any other investigational agents within 28 days prior to enrollment in this studyPatients who have previously received FOLFIRI with irinotecan dose escalationOther concurrent cancer or prior treatment for other carcinomas within the last 5 years, except curatively treated nonmelanoma skin cancer, superficial bladder tumors, and cervical cancer in situExtended field radiotherapy within 28 days or limited radiotherapy within 14 days prior to randomizationMajor surgery within 28 days prior to the start of study treatment (diagnostic biopsy, laparotomy and line placement is not considered as major surgery)Uncontrolled intercurrent illness including, but not limited to, ongoing or active infection, symptomatic congestive heart failure, myocardial infarction in the past 12 months, active gastrointestinal bleeding, central nervous system disorders or psychiatric illness/social situation that would limit compliance with study requirements or judged to be ineligible for the study by the investigatorHistory of myocardial infarction, deep venous or arterial thrombosis, or cerebrovascular accident during the last 6 monthsUncontrolled cardiac arrhythmias, unstable angina, or new-onset angina within 3 months prior to study entryUncontrolled hypertension despite optimal management (systolic blood pressure >150 mmHg or diastolic pressure >90 mmHg)Patients with known central nervous system metastasesHaving received any investigational agents or participated in any investigational drug study within 4 weeks prior to study enrollmentPregnant or breast-feeding female (a pregnancy test must be performed on all female patients who are of child-bearing potential within 7 days of treatment initiation, and the result must be negative)Inability to take oral medicationPoor compliance as judged by the investigator

### Genotyping

DNA is extracted from 4 mL of peripheral blood of patients with a PUREGENE® DNA isolation kit (Gentra Systems, Inc., Minneapolis, MN, USA). The genomic DNA extracted is then analyzed using direct sequencing to determine the *UGT1A1* promoter genotype. The primers are designed by primer 3 free software (http://primer3.wi.mit.edu), and the sequence of the forward primer is 5-AGT-CACGTGACACAGTCAAACA-3 and the reverse primer is 5-CTTTGCTCCTGCCAGAGGTT-3. The polymerase chain reaction (PCR) volume is 40 μL and the PCR conditions for the *UGT1A1* are as follows: 94.0 °C for 5 min; annealing for 20 s at 67.5 °C; primer extension for 20 s at 72.0 °C; and final extension for 10 min at 72.0 °C. A fragment analysis of the PCR products is conducted to verify the genotypes using the automated capillary electrophoresis on the ABI PRISM 310 Genetic Analyzer (Applied Biosystems, Foster City, CA, USA), and the genotypes are analyzed using GeneScan and Genotyper software (Applied Biosystems) [10].

### Interventions

#### Control group

The treatment for the control group will be oral regorafenib monotherapy at the dosing schedule of 120 mg once daily for the first 3 weeks of each 4-week cycle, without *UGT1A1* genotyping. If any regorafenib-related AEs greater than grade 3 develop, regorafenib will be stopped until the encountered AEs recover and the dose of regorafenib will be reduced by 40 mg daily.

#### Study group

The treatment for the study group will be oral regorafenib 120 mg once daily for the first 3 weeks of each 4-week cycle as described above and additional infusion of a FOLFIRI regimen. If any regorafenib-related AEs greater than grade 3 develop, regorafenib will be stopped until the encountered AEs recover and the dose of regorafenib will be reduced by 40 mg daily. According to the *UGT1A1* genotypes, the study group is further divided into the three following subgroups.

##### Subgroup 1: UGT1A1*1/*1 genotype

Oral regorafenib will be administered at a dose of 120 mg once daily for the first 3 weeks of each 4-week cycle. A FOLFIRI regimen will be initiated at a dose of 180 mg/m^2^ irinotecan and 200 mg/m^2^ LV intravenous (IV) infusion over 2 h followed by 5-FU (2800 mg/m^2^ as an IV infusion over a 46-h period). If no FOLFIRI-related AEs greater than grade 3 are observed after two cycles of each dose of irinotecan, the dose of irinotecan will be escalated in steps of 30 mg/m^2^. If any FOLFIRI-related AEs greater than grade 3 are encountered, the dose of irinotecan will be reduced by 30 mg/m^2^ or back to the previous dose and be held at that dose at the next cycle. The maximum dose of irinotecan for subgroup 1 is 260 mg/m^2^.

##### Subgroup 2: UGT1A1*1/*28 genotype

Oral regorafenib will be administered at a dose of 120 mg once daily for the first 3 weeks of each 4-week cycle. A FOLFIRI regimen will be initiated at a dose of 180 mg/m^2^ irinotecan and 200 mg/m^2^ LV IV infusion over 2 h followed by 5-FU (2800 mg/m^2^ as an IV infusion over a 46-h period). If no FOLFIRI-related AEs greater than grade 3 are observed after two cycles of each dose of irinotecan, the dose of irinotecan will be escalated in steps of 30 mg/m^2^. If any FOLFIRI-related AEs greater than grade 3 are encountered, the dose of irinotecan will be reduced by 30 mg/m^2^ or back to the previous dose and be held at that dose at the next cycle. The maximal dose of irinotecan for subgroup 2 is 240 mg/m^2^.

##### Subgroup 3: UGT1A1*28/*28 genotype

Oral regorafenib will be administered at a dose of 120 mg once daily for the first 3 weeks of each 4-week cycle. A FOLFIRI regimen will be initiated at a dose of 120 mg/m^2^ irinotecan and 200 mg/m^2^ LV IV infusion over 2 h followed by 5-FU (2800 mg/m^2^ as an IV infusion over a 46-h period). If no FOLFIRI-related AEs greater than grade 3 are observed after two cycles of each dose of irinotecan, the dose of irinotecan will be escalated in steps of 30 mg/m^2^. If any FOLFIRI-related AEs greater than grade 3 are encountered, the dose of irinotecan will be reduced by 30 mg/m^2^ or back to the previous dose and be held at that dose at the next cycle. The maximal dose of irinotecan for subgroup 3 is 180 mg/m^2^.

#### Stopping treatment/other medications

All treatment will be stopped in the event of patient withdrawal, disease progression, or unacceptable AEs, which are defined as nonhematological grade 4 AEs, no recovery from grade 3 AEs after two consecutive dose reductions, or no recovery after a 2-week treatment delay.

Throughout the study period, participants should not receive other cytotoxic or biological treatments for mCRC. If concomitant treatments are considered necessary based on investigator discretion, the product package insert should be referenced for contraindications and all concomitant treatments should be recorded on the relevant case report form (CRF) page.

### Outcome measurements

#### Primary outcome

The treatment response will be radiologically assessed every 2 months with computed tomography or magnetic resonance imaging. Objective responses will be classified according to RECIST and optimal treatment responses will be recorded. The primary endpoint is PFS, which is defined as the time from initiation of study treatment to first radiological progression or tumor-related death, whichever comes first.

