#### Secondary outcome

Secondary outcomes will be as follows:
OS is defined as the time from initiation of study treatment to death due to any causeDCR is defined as the percentage of patients whose best response was not progressive disease (i.e., complete response, partial response or stable disease)Time to progression is defined as the time (in days) from the start of study treatment to the first documented disease progressionDuration of treatment is defined as the time interval from the start of study treatment to the day of permanent discontinuation (including death); mean dose and reasons for treatment discontinuation or dose modification will be recorded

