### Sample size estimation

Using a per-protocol two-sided α of 0.025, a 2:1 randomization between regorafenib plus FOLFIRI dose escalation and regorafenib, and a median PFS of 3.2 months in the regorafenib group [9], the study would have 90% power to detect assumed median PFS of 7.0 months with regorafenib plus FOLFIRI [3]. The assumption of overall probability of events is 0.77 (10 progressions at the end of the study out of 13 in total) [9]. The calculated sample size is 121 patients. Considering a 20% drop-rate, a total of 153 patients should be enrolled into the study, with 102 assigned to the study group (FOLFIRI plus regorafenib group) and 51 to the control group (regorafenib monotherapy group).

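### PFS, OS and time to progression start at first treatment rather than at randomisation, so in this open-label trial the comparison is of patients who started, not of the groups as randomised

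*Protocol article*

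**What the plan says.** Under Primary outcome, PFS is "defined as the time from initiation of study treatment to first radiological progression" or tumour-related death. Under Secondary outcome, "OS is defined as the time from initiation of study treatment to death" from any cause, and time to progression also runs from the start of study treatment. Duration of treatment has the same origin, which is natural for that endpoint.

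Under Trial design, "Neither the investigators nor the patients are masked to treatment allocation".

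The arms differ in what has to be known before treatment. Under Control group, regorafenib is given "once daily for the first 3 weeks of each 4-week cycle, without *UGT1A1* genotyping". Under Study group, according to UGT1A1 "genotypes, the study group is further divided into the three following subgroups", and the three subgroup sections set the irinotecan starting dose by genotype. The regorafenib starting dose is the same in the control group and in all three genotype subgroups.

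Under Study participants, "informed consent will be obtained from all participants before randomization". Table 1 (Participant timeline) places consent and randomisation at time point 0 and the baseline tumour assessment at 2 weeks before. It has no row for genotyping. The Genotyping section does not say when the blood is drawn or how long the result takes. The article gives no maximum interval from randomisation to first dose and no time origin for a patient who is randomised but never treated.

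**The concern.** Randomisation makes the arms comparable at the moment of allocation. A clock that starts later, at an event that patients and investigators can influence once they know the allocation, gives up part of that protection. Three things follow from the definitions as written:

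- A patient who is allocated and never starts has no PFS, OS or time-to-progression value. Naming an all-randomised analysis set elsewhere would not supply one, because the endpoint definition itself has no time zero for that patient.
- Deaths and withdrawals between allocation and first dose are not represented.
- The distance between randomisation and time zero may differ by arm, because only the study arm has a genotype-dependent component to prepare.

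The possible biases point in opposite directions. Losing early failures or refusals mainly from the study arm would favour that arm. Tumour growth before a later time zero, against a baseline scan taken before randomisation, would count against it. The net direction cannot be predicted, which is a reason to settle the matter in the definition.

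**Working it through.** **1. The plan's own figure.** Inputs from Sample size estimation: medians 3.2 and 7.0 months, two-sided α 0.025, power 90%, allocation 2:1, event probability 0.77, drop rate 20%.

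- HR = 3.2/7.0 = 0.457.
- Schoenfeld events = (z for 0.9875 + z for 0.90)² / [(2/3)(1/3)(ln HR)²] = (2.241 + 1.282)² / (0.2222 × 0.6127) = 91.2, so 92 events.
- 92/0.77 = 119.5, so 120 patients; the article states 121.
- 121/0.80 = 151.3, so 152; rounded up to a multiple of 3 for 2:1 allocation this is 153, as stated.

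The formula does not use the time origin. On the stated medians, moving the origin to randomisation leaves the sample size as it is.

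**2. Is there a gap, and does it differ by arm?** Genotyping is described for the study arm only and consent and randomisation share time point 0, so the most natural reading is that genotyping follows allocation. But only irinotecan depends on the result. If regorafenib counts as the start of study treatment and begins at once, the gap could be nil. The lag is therefore an assumption: 7 or 14 days in the study arm, none in the control arm.

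**3. What would be lost in such a gap?** PFS events are radiological progression or tumour-related death. Imaging is every 2 months (Primary outcome) or every 8 weeks (Table 1), so no scan is scheduled within a 1- or 2-week gap. Progression in that time would normally show at the first on-study scan. What is lost is deaths and patients who never start.

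Deaths, with the 8.8-month regorafenib median OS of the Asian trial cited in the Background and a constant hazard:

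- hazard = ln 2/8.8 = 0.0788 per month
- 7 days: 1 − exp(−0.0788 × 7/30.44) = 1.8%, and 102 × 0.018 = about 2 patients
- 14 days: 1 − exp(−0.0788 × 14/30.44) = 3.6%, and 102 × 0.036 = about 4 patients

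Refusals and withdrawals come on top; the article gives nothing from which to estimate them.

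**4. Would the hazard ratio move?** Suppose the treatment has no effect and all first PFS events in the gap are removed from the study arm.

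- With constant hazards the HR stays at about 1.00, because an exponential survival time has no memory.
- With unequal prognosis (gamma frailty with variance 1, median 3.2 months), a simulation gave about 0.93 for a 14-day and 0.87 for a 28-day lag, in favour of the study arm.

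The second result needs both the frailty assumption and the removal of progressions that no scheduled scan would record. It shows that a bias can arise; it does not estimate one for this trial.

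**The case against.** The strongest reply is that both arms share one nominal origin, that no delay is documented, and that handling of untreated patients is commonly left to a full protocol or analysis plan not shown here. The first two parts stand and limit what can be claimed. The third stands for the choice of analysis population, but not for the origin: the article fixes it in the definition of the primary endpoint and two secondary endpoints.

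A reader might infer more than the documents support:

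- **That the study arm waits for its genotype before starting.** No section says so, and the regorafenib starting dose does not depend on genotype. The interval may differ; it is not shown to.
- **That about 5 or 10 of 102 first events vanish.** The control PFS hazard, ln 2/3.2 = 0.2166 per month, gives 4.9% in 7 days and 9.5% in 14. It counts progressions that no scheduled scan would record in the gap, so it overstates the loss. Even the death figures are probably high, since eligibility requires performance score 0–1 and life expectancy above 12 weeks.
- **That the planned drop-out shows the scale.** The article says "Considering a 20% drop-rate, a total of 153 patients should be enrolled into the study". This is only an inflation of the sample size; nothing links it to non-starting or to one arm.
- **That the bias could never be examined.** Randomisation is a scheduled item in Table 1. If its date is kept, the lag can be compared by arm and treated patients re-analysed from randomisation. Patients who never start can be included only if they are followed.

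**Conclusion.** The point holds in limited form. The text establishes a post-randomisation origin for PFS, OS and time to progression, open allocation, genotype-dependent treatment in one arm only, and no time zero for patients who never start. As defined, the endpoints compare patients who started treatment.

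The size and direction of any bias are unknown. The 2 or 4 deaths among 102 study-arm patients rest on an assumed 7- or 14-day lag confined to that arm, a constant hazard and the 8.8-month median; with no lag the figure is zero. The case for change does not depend on these numbers: even with equal lags, a patient who never starts has no endpoint value in an unmasked trial. The definitions should be changed, since the change is specific, reduces the risk of bias and costs little.

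**What to change.** - Define PFS, OS and time to progression from the date of randomisation, and analyse all randomised patients in the arm to which they were allocated.
- State that the 8-weekly imaging is counted from randomisation in both arms. Table 1 already puts time 0 at allocation, so this may only make explicit what is intended.
- Keep treatment start as the origin for duration of treatment and for safety only.

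The cost is mainly wording. The sample-size calculation (92 events; 120 patients against the stated 121; 153 enrolled) is unchanged on the stated medians. Patients who never start must be followed for progression and survival. Times will include any short pre-treatment interval: an assumed 7 or 14 days is 3% or 7% of the 7.0-month study-arm median. That interval is part of what allocation to the arm entails. An analysis from treatment start can be kept as supportive.

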In our preliminary, retrospective and observational study, in which 41 patients with mCRC were treated with regorafenib plus irinotecan dose-escalated FOLFIRI as a third- or fourth-line setting, median PFS was 6.0 months, median OS was 12.0 months and DCR was 58.5% [13]. Compared to the CORRECT and CONCUR studies, the oncological outcomes were satisfactory and treatment-related AEs were acceptable. To the best of our knowledge, there is no prospective study concerning the reintroduction of irinotecan for patients with mCRC; reintroduction of dose-escalated irinotecan for those previously treated with no irinotecan escalation may show similar results.

This is a multicenter, randomized clinical trial. There are no randomized clinical trials concerning the combination of regorafenib and irinotecan dose-escalated FOLFIRI for mCRC launched so far. Although there are aforementioned strengths to this study, this study is based on the results of a previous small, retrospective analysis and the rates of AEs of such a combination lead to some weaknesses.

This trial combines regorafenib, a targeted agent, with irinotecan dose-escalated FOLFIRI that may provide an alternative salvage treatment for previously treated mCRC.

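### The primary endpoint called PFS counts only tumor-related deaths, so a non-tumor death before progression is not an event and event status depends on an attribution that masking does not protect

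*Protocol article*

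**What the plan says.** Under Primary outcome, the protocol article starts the PFS clock at the beginning of study treatment and stops it at "first radiological progression or tumor-related death, whichever comes first". No other section widens this.

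Under Secondary outcome, OS counts deaths of every cause. Time to progression is listed separately and "is defined as the time (in days) from the start of study treatment to the first documented disease" progression, so it counts no deaths.

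Under Trial design: "Neither the investigators nor the patients are masked to treatment allocation".

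Under Study group, the experimental arm receives the control arm's regorafenib schedule "as described above and additional infusion of a FOLFIRI regimen". In each genotype subgroup, when the toxicity condition is met, "the dose of irinotecan will be escalated in steps of 30 mg/m^2", up to a subgroup maximum. The Discussion concedes that "the rates of AEs of such a combination lead to some weaknesses". It gives no rates of toxic or other non-tumor death for either arm.

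**The concern.** Progression-free survival is meant to treat any death before progression as a failure. Here a fatal toxicity, infection or other non-tumor death before progression is not a failure. The wording is not loose shorthand: the article uses an all-cause definition for OS and a narrower one for PFS.

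Three things are at stake.

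- **What is estimated.** The primary endpoint differs from time to progression only by deaths classed as tumor-related before documented progression. Among the time-to-event efficacy endpoints, only OS would count a toxic death as a failure.
- **Who or what decides an event.** Whether a death without progression counts depends on its assigned cause, in a trial where treatment is known. Imaging is every 2 months and the planned control median PFS is 3.2 months, so a death before the first on-study scan is settled by attribution alone.
- **Possible imbalance.** One arm is the other plus escalating cytotoxic chemotherapy. If that adds non-tumor deaths, those are the deaths the definition removes.

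**Working it through.** **1. The plan's own figure.** Inputs from Sample size estimation: "Using a per-protocol two-sided α of 0.025, a 2:1 randomization between regorafenib plus FOLFIRI dose escalation and regorafenib", "a median PFS of 3.2 months in the regorafenib group", 7.0 months in the study group, 90% power and event probability 0.77.

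- Planned HR (exponential PFS) = 3.2/7.0 = 0.457; ln(0.457) = −0.783.
- Schoenfeld events = (2.241 + 1.282)² / [(1/3)(2/3) × 0.783²] = 91.2, so 92.
- 92/0.77 = 119.5, so 120 patients, against 121 stated. 121/0.80 = 151.25, so 152, raised to 153 for a 102 + 51 split.

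The stated size is reproduced to within one patient, so the point does not rest on a sample size error. Events expected from the stated number: 0.77 × 121 = 93.

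**2. Effect of leaving out non-tumor deaths.** Let f be the share of all-cause PFS events that are non-tumor deaths without progression. The documents give no value, so every f below is an assumption. With f constant over time, the hazard of a counted event in an arm is its all-cause hazard × (1 − f). Hence

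apparent HR = true HR × (1 − f_combination)/(1 − f_control).

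This applies when such deaths simply leave the risk set. The article does not say how they are handled.

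**3. False-win rate at a true HR of 1.** The shift in Z is ln(apparent HR) × √(93 × 2/9) = ln(apparent HR) × 4.546. The chance of a significant result for the combination is Φ(−c − shift). Here c = 1.960 for P < 0.05 (Statistical methods) and c = 2.241 for two-sided 0.025 (Sample size estimation). Both are shown because the article states both thresholds.

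Worked case, 3% control and 10% combination: 0.90/0.97 = 0.928; ln = −0.0749; shift = −0.34; Φ(−1.960 + 0.34) = 5.3%; Φ(−2.241 + 0.34) = 2.9%.

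| Assumed share, control / combination | Apparent HR | False win at P < 0.05 | False win at two-sided 0.025 |
|---|---|---|---|
| 5% / 5% (equal) | 1.00 | 2.5% | 1.25% |
| 2% / 5% | 0.97 | 3.4% | 1.8% |
| 0% / 5% | 0.95 | 4.2% | 2.2% |
| 3% / 10% | 0.93 | 5.3% | 2.9% |
| 2% / 15% | 0.87 | 9.5% | 5.5% |
| 10% / 5% (reversed) | 1.06 | 1.4% | 0.6% |

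**4. Size beside the planned effect.** If the all-cause HR were the planned 0.457, shares of 3%/10% would make it appear as 0.457 × 0.928 = 0.42, and 0%/5% as 0.457 × 0.95 = 0.43. Equal shares leave the HR alone but lengthen both medians: at 5%/5%, 3.2/0.95 = 3.37 and 7.0/0.95 = 7.37 months.

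**The case against.** The strongest reply is that the harm is assumed. The article reports no non-tumor death rate in either arm, and an adverse-event rate is not a rate of toxic death before progression. The same Discussion that names adverse events as a weakness also calls treatment-related events acceptable in the preliminary series of 41 patients. Equal shares give no bias in the HR, an excess in control reverses it, and against a planned HR of 0.457 a factor of 0.93 or 0.95 is small. All of this stands. It limits the claim about direction and size, but not the defect in the definition.

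A reader might infer more than the text supports:

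- **That the combination is favoured.** The add-on design makes this the likelier direction, but no figure in the article establishes it.
- **That non-tumor deaths are censored.** The article says only what counts as an event. Censoring and competing-event treatment are both open, and such detail may sit in the full protocol or SAP. Either way these deaths are not PFS events.
- **That unmasked investigators rule on cause of death.** The article says investigators and patients are unmasked. It does not say who attributes deaths.
- **That the endpoint is time to progression under another name.** The two are close, but tumor-related deaths between scans count for one and not the other. In third- or fourth-line patients scanned every 2 months some may occur, and the article does not say how many.

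**Conclusion.** The concern holds as a defect in the stated event definition. As written, the primary endpoint depends on cause of death and is not progression-free survival. In an open-label trial, that makes event status turn on an attribution without the protection of masking. This follows from the text and needs no assumption.

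Bias toward the combination is plausible but unproven. Its size rests on assumed shares that are constant over time, on 93 counted events, and on non-tumor deaths leaving the risk set. Over the unequal shares tried with an excess in the combination arm, a true HR of 1 would appear as 0.97 to 0.87. At 3%/10% the one-sided error roughly doubles at either threshold. At equal shares there is no HR bias, and with the excess in control it runs the other way.

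**What to change.** Define the primary endpoint as time from the existing start point to the earlier of radiological progression (RECIST 1.1) and death from any cause. Leave time to progression as the secondary endpoint that does not count deaths.

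The text change is one phrase, and no new data are needed because all deaths are already required for OS and survival is followed every 8 weeks. The procedural cost is larger. The trial is registered and has been recruiting since 1 April 2019, so the change is a protocol amendment. Under Trial status it needs Institutional Review Board approval and communication to investigators and registries. Since treatment is unmasked, the amendment should record its date and reason. The PFS hazard ratio may look slightly less favourable to the combination.
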